### Intervention

#### Moving cupping intervention

The cup has the texture of transparent glass. For convenience, different cup sizes will be selected according to the site of the patient’s skin lesions (Fig. 2).

**Fig. 2 Fig2:**
[figure not shown]
Different cups used for the intervention group and the control group when implementing moving cupping therapy. **a** The cups used for the intervention group can produce a negative pressure adsorption force when the air in the cup is burned. **b** The cup used for the placebo group has a special perforation design, and no negative pressure adsorption was formed after combustion

Moving cupping involves standardized manipulations. First, Vaseline is applied to the skin lesion area. Using the flashing method, a 95% ethanol-soaked cotton ball is held with tweezers and the cup is held upside-down. After the cotton ball is ignited, it is immediately moved down inside the cup and removed; the cup is then quickly placed on the skin lesion area. After using the cup to absorb the skin lesion area, the cup body is held in one hand and pushed and pulled according to the skin lesion area while applying light force, such that the skin of the treatment area turns purple. Even force is applied when pushing the cup to prevent the cup from falling off due to air leakage. This is repeated on the skin lesion area 30 times [29]. The cup is changed five times per push and pull, with an interval of no more than 10 seconds. This will be performed once every other day for 4 weeks.

#### Moving cupping placebo

A special perforated cup made of the same material as that used for the intervention group will be selected and used during the same manipulation method as described for the intervention. Due to the perforated design, the fire cannot burn the air in the cup; therefore, it cannot form a negative pressure adsorption force. This simulates the form of moving cupping therapy without the therapeutic effects (Fig. 2).

#### Basic treatment

Increase moisturizing of the skin: As a basic treatment, the use of a moisturizer at all times is mandatory. The moisturizer should be applied to the skin areas that are free from erosion and exudation, as well as the dry non-lesion areas. A soft, fragrance-free moisturizer should be used. Yuze moisturizer will be recommended to patients with sensitive dry skin.Standard bath: Generally, patients should rinse quickly with warm water (35–39 °C) once per day for approximately 5 minutes. Moisturizer should be applied within 2 minutes of bathing to avoid dehydration of the epidermis. The use of alkaline detergents to clean the skin should be avoided.Avoidance of induced and aggravated factors: For some patients, certain foods can aggravate or induce disease. These foods should be avoided.Some patients may have food allergies. When food allergies are identified, such foods should be avoided to prevent inducing or aggravating the condition.Maintain a reasonably healthy lifestyle: Patients should avoid staying up late and becoming overly stressed. Spicy, irritating foods should be avoided, and appropriate exercise should be performed. Patients should attempt to maintain normal bowel movements.

### Measurement

#### Baseline measurements

Vital signs and disease severity will be monitored by physical examinations, biochemical examinations, and various evaluation indices before treatment. Foods that cause allergic reactions will be identified by food allergen testing. Data from these measures will be used as baseline moving cupping therapy data.

### Examination during the interview

#### Interview plan

All patients will be interviewed at weeks 1, 2, 3, and 4 during treatment. They will be reminded of the interview by phone 1 day before it is scheduled to occur. During weeks 1, 2, 3, and 4 of treatment, the psoriatic lesions will be measured by PASI, PGA, BSA, and TCMSSS, and the DLQI and VAS will be used to assess the quality of life and psychological status, and degree of pruritis, respectively. Their moisturizing, diet, and bathing habits will be monitored via patient diaries. In addition, during weeks 6 and 8 of the follow-up, the PASI, PGA, BSA, and VAS will be recorded again to evaluate the efficacy of moving cupping. Possible adverse events and combined medications should be accurately recorded at all of these time points.

### Examination during follow-up

#### Follow-up plan

All patients will be followed-up by phone at weeks 6 and 8 after treatment. During each follow-up session, the treatment effects will be assessed using the PASI, PGA, BSA, and VAS.

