**Methods:**

A multicenter, two-arm parallel group, single-blind, randomized, controlled trial will be conducted at six hospitals in China between August 1, 2019 and December 31, 2021. A total of 122 adult patients (aged 18–65 years) who meet the inclusion criteria are being recruited. Participants will receive either basic treatment combined with moving cupping therapy or basic treatment combined with moving cupping placebo. The treatment cycle will be 4 weeks, and the efficacy of treatment will be assessed weekly by the Psoriasis Area and Severity Index during the treatment period and follow-up visits at weeks 6 and 8. The body surface area, physician’s global assessment, Dermatology Life Quality Index, patient-reported quality of life, visual analog scale, Traditional Chinese Medication syndrome scoring scale, combined medication, and adverse events will also be recorded and compared to the relative baseline values.

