## Methods

### Study design

The proposed study is designed as a prospective, multicenter, two-arm parallel group, single-blind RCT. Patients with plaque psoriasis will be randomly assigned to the treatment group (moving cupping) or the placebo group (sham moving cupping). Eligible participants will receive 4 weeks of treatment and a total of 8 weeks of follow-up (Table 1).

**Table 1 Tab1:** Study schedules of enrollment, intervention, and assessment

	Study period							
	Enrollment	Allocation	Treatment period				Follow-up period	
Time point	-week_1_	0	week_1_	week_2_	week_3_	week_4_	week_6_	week_8_
Enrollment								
Eligibility screen	**×**							
Informed consent	**×**							
List other procedures	**×**							
Allocation		**×**						
Interventions:								
Basic treatment plus moving cupping therapy								
Basic treatment plus moving cupping placebo								
Assessments:								
PASI	**×**	**×**	**×**	**×**	**×**	**×**	**×**	**×**
BSA	**×**	**×**	**×**	**×**	**×**	**×**	**×**	**×**
PGA	**×**	**×**	**×**	**×**	**×**	**×**	**×**	**×**
DLQI		**×**	**×**	**×**	**×**	**×**		
VAS		**×**	**×**	**×**	**×**	**×**	**×**	**×**
TCMSSS		**×**	**×**	**×**	**×**	**×**		
Vital signs	**×**	**×**	**×**	**×**	**×**	**×**		
Routine blood test	**×**					**×**		
Blood biochemical test	**×**					**×**		
Routine urine test	**×**					**×**		
Food allergen test	**×**							
Combined medications	**×**	**×**	**×**	**×**	**×**	**×**		
Pregnancy test	**×**							
Physical examination	**×**					**×**		
Adverse event		**×**	**×**	**×**	**×**	**×**		
Serious adverse events		**×**	**×**	**×**	**×**	**×**		

BSA, body surface area; DLQI, Dermatology Life Quality Index; PASI, Psoriasis Area and Severity Index; PGA, Physician’s Global Assessment; PR-QoL, patient-reported quality of life; TCMSSS, Traditional Chinese Medicine syndrome scoring scale; VAS, visual analog scale

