### Primary parameters

PASI: Incorporates the extent of psoriasis at four anatomical sites by evaluating signs of erythema, scale, and elevation. PASI scores range from 0 to 72. The primary outcome of the RCT is the proportion of patients with a reduction in PASI scores of ≥ 75% compared to baseline at the 4‑week follow-up visit [27].

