### Secondary parameters

The secondary parameters of this study include the following:
PGA: The PGA is scored using a 5-point scale reflecting the overall degree of erythema, infiltration, and desquamation across all psoriatic lesions [27].BSA: The BSA involved in psoriasis is estimated by fingerprinting, whereby the entire palm of the patient represents approximately 1% of the total BSA. The number of handprints on the psoriatic skin on a body part is used to determine the extent to which the body part is affected by psoriasis (%) [27].DLQI: The DLQI is a participant-reported questionnaire used to measure the health-related quality of life of adults with skin diseases. Scores range from 0 to 30, with a higher score indicating a greater impact on the participant’s quality of life [30].VAS: The VAS is used to measure lesion pruritus from 0 to 100 mm at each visit (with 0 indicating no pruritus and 100 indicating maximum pruritus) [31].TCMSSS: According to the different TCM syndromes, comprehensive evaluations will be performed to determine the conditions of the tongue, pulse, and skin. The score ranges from 0 to 6 [32].

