### Data collection and management

Each center will designate a full-time researcher, and data collection will be performed in a dermatology clinic using a unified data collection system (provided by Nanjing Ningqi Medical Technology Co., Ltd. Data Management Center, Nanjing, China). With the exception of the DLQI, R-QoL, and VAS, the evaluation indicators will be completed by data collectors. All data collectors will be trained to implement the PASI and other scales.

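### PASI, PGA and BSA at the two post-treatment points are to be assessed at phone sessions, and those sessions are dated from a different origin than in Table 1

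*Protocol article*

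**What the plan says.** The Follow-up plan sets both the mode and the timing of post-treatment contact: "All patients will be followed-up by phone at weeks 6 and 8 after treatment". The next sentence says what is measured there: "During each follow-up session, the treatment effects will be assessed using the PASI, PGA, BSA, and VAS".

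Other parts of the article describe something different:

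- **Mode.** The abstract's methods paragraph refers to "follow-up visits at weeks 6 and 8". Data collection and management says that "data collection will be performed in a dermatology clinic using a unified data collection system". It assigns every scale except the patient-completed ones (DLQI, quality of life, VAS) to data collectors who have been trained in PASI and the other scales.
- **Measures.** Primary parameters describes PASI thus: "Incorporates the extent of psoriasis at four anatomical sites by evaluating signs of erythema, scale, and elevation". Secondary parameters says: "The PGA is scored using a 5-point scale reflecting the overall degree of erythema, infiltration, and desquamation across all psoriatic lesions". BSA is obtained by counting handprints over the affected skin.
- **Timing.** Table 1 runs on one axis from allocation at 0, with weeks 1 to 4 as treatment and weeks 6 and 8 as follow-up. The sentence that introduces it reads: "Eligible participants will receive 4 weeks of treatment and a total of 8 weeks of follow-up". The Interview plan also names weeks 6 and 8, but as weeks of the follow-up.
- **Primary endpoint.** Primary parameters places PASI-75 at a four-week follow-up visit, whereas Table 1 classes week 4 as treatment.

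**The concern.** Two instructions in one short section cannot both be carried out. A telephone call gives the assessor no view of redness, scaling or plaque thickness, and no way to lay handprints over the skin. The article describes no photograph, video or self-assessed version of PASI, PGA or BSA. A site following the section literally would have to enter values that are not the scales the article defines.

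Weeks 6 and 8 are the only assessments after treatment stops. They are therefore all the evidence from these three scales on whether any effect lasts, and the Interview plan says they are taken to evaluate efficacy.

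The wording on timing adds a second problem. With six hospitals enrolling, one could follow Table 1 and another the Follow-up plan, and values labelled alike would then come from different times since the last treatment.

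**Working it through.** The plan gives no figure for this point to reproduce. The sample size (51 per group, 61 after allowance for loss, 122 in total) does not depend on it. The check sets the sections side by side and counts weeks.

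**1. Can each follow-up measure be taken by phone, as the article defines it?**

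| Measure | What the article's definition needs | Who completes it | Obtainable by phone? |
|---|---|---|---|
| PASI | Erythema, scale and elevation at four sites | Trained data collector | No |
| PGA | Erythema, infiltration and desquamation over all lesions | Trained data collector | No |
| BSA | Handprint count on affected skin | Trained data collector | No |
| VAS | Pruritus, 0 to 100 mm | Patient | In principle, yes |

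Three of the four measures fail.

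**2. How much of the schedule is affected?** Table 1 marks PASI, BSA and PGA after baseline at weeks 1, 2, 3, 4, 6 and 8, which is 6 points. Those in the follow-up period are weeks 6 and 8, which is 2 points.

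- Share of post-baseline points: 2/6 = 33%.
- Share of post-treatment points: 2/2 = 100%.

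These are counts of scheduled assessments. They do not estimate bias or loss of power.

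**3. When do the sessions fall?** Treatment lasts 4 weeks from allocation.

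| Source | Study weeks from allocation | Weeks after end of treatment |
|---|---|---|
| Table 1 and abstract | 6 and 8 | 6 − 4 = 2 and 8 − 4 = 4 |
| Follow-up plan, read literally | 4 + 6 = 10 and 4 + 8 = 12 | 6 and 8 |

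The gap is 10 − 6 = 4 weeks and 12 − 8 = 4 weeks. The Study design sentence fits either reading. If its 8 weeks include treatment, participation ends at week 8. If they follow treatment, it ends at 4 + 8 = week 12.

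**4. Is the primary endpoint touched?** Table 1 and the Interview plan both schedule PASI at week 4, within treatment and apart from the phone follow-up. Read there, PASI-75 is not a phone score.

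**The case against.** **The phone may serve only as a reminder.** The Interview plan does use the phone that way, for a call one day before each interview. The Follow-up plan is worded differently: the follow-up itself is by phone, and scoring is placed in that session. This objection does not stand.

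**The sites may hold clinic visits anyway.** The abstract and the data collection section point that way. If so, the fault is a contradiction to be reconciled, and no data are lost. This stands, and it makes the invalidity conditional on the Follow-up plan being followed.

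**The article is condensed, and the full protocol may describe remote scoring.** That is possible. But the point does not rest on missing detail. The article states a mode that does not fit its own definitions or its own account of where data are collected.

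**The timing conflict is one phrase against an explicit schedule.** This is largely fair. Table 1 and the abstract agree, and the Study design sentence cites Table 1, so its 8 weeks may simply be the table's span. Only the Follow-up plan clearly yields weeks 10 and 12. It is, however, the section that governs these contacts.

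A reader might also infer three stronger things that the text does not support:

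- *That the primary PASI could be a phone score.* This needs two time origins at once. The four-week follow-up visit would have to mean four weeks after treatment (4 + 4 = study week 8), while the phone contact is dated from allocation (also week 8). If the phone contacts are dated after treatment, they fall at weeks 10 and 12 and none falls at week 8.
- *That all post-treatment efficacy data are lost.* VAS is patient-reported and is also taken at weeks 6 and 8.
- *That phone and clinic scores will be pooled in the repeated-measures model.* Statistical analysis says only that quantitative variables with repeated measures go to general linear models. It does not say which weeks enter, and its list of quantitative variables includes neither PGA nor BSA.

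**Conclusion.** The Follow-up plan is wrong as written and should be fixed. If it is followed, PASI, PGA and BSA at both post-treatment points would not be valid measurements. If clinic visits are held instead, what remains is a contradiction in the text.

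The conflict over timing is also real, at 4 weeks for each contact, although Table 1 and the abstract make the intended schedule fairly clear. The primary endpoint needs only a clearer label, and no sample-size or power figure changes.

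The conclusion rests on the article's own definitions of the three scales and on the absence of any described remote method of scoring them.

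**What to change.** 1. **Mode.** Reconcile the Follow-up plan with the abstract, Table 1 and Data collection and management. State that PASI, PGA and BSA at the follow-up points are scored in clinic by the trained data collectors.
2. **Phone contacts.** Where only phone contact is made, collect VAS alone. Do not report or analyse PASI, PGA or BSA from that contact.
3. **Time origin.** Date both points as study weeks 6 and 8 from allocation, and remove the count from the end of treatment. Reword the Study design sentence so that its 8 weeks match Table 1, and use the same origin in the Interview plan.
4. **Primary time point.** In Primary parameters, label it week 4 (end of treatment), as in Table 1.

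The cost is amendment wording plus two clinic visits per participant, which the abstract already calls visits. Where those visits cannot be held, the cost is the loss of PASI, PGA and BSA at weeks 6 and 8, so that VAS would be the only follow-up measure left.

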### Primary parameters

PASI: Incorporates the extent of psoriasis at four anatomical sites by evaluating signs of erythema, scale, and elevation. PASI scores range from 0 to 72. The primary outcome of the RCT is the proportion of patients with a reduction in PASI scores of ≥ 75% compared to baseline at the 4‑week follow-up visit [27].

### Secondary parameters

The secondary parameters of this study include the following:
PGA: The PGA is scored using a 5-point scale reflecting the overall degree of erythema, infiltration, and desquamation across all psoriatic lesions [27].BSA: The BSA involved in psoriasis is estimated by fingerprinting, whereby the entire palm of the patient represents approximately 1% of the total BSA. The number of handprints on the psoriatic skin on a body part is used to determine the extent to which the body part is affected by psoriasis (%) [27].DLQI: The DLQI is a participant-reported questionnaire used to measure the health-related quality of life of adults with skin diseases. Scores range from 0 to 30, with a higher score indicating a greater impact on the participant’s quality of life [30].VAS: The VAS is used to measure lesion pruritus from 0 to 100 mm at each visit (with 0 indicating no pruritus and 100 indicating maximum pruritus) [31].TCMSSS: According to the different TCM syndromes, comprehensive evaluations will be performed to determine the conditions of the tongue, pulse, and skin. The score ranges from 0 to 6 [32].

### Safety monitoring

All participants will be advised to remain under supervision in the clinical research unit for 15 minutes after treatment. In addition, data of the participants will be monitored by the research team to detect any adverse events throughout the study, such as skin damage or potential allergies. All potential adverse events will be recorded. If any participant experiences an adverse effect due to trial participation, they will receive free treatment and compensation accordingly. If any concerns of the participants are identified during screening or clinical assessment, further clinical evaluations and/or investigations will be performed immediately. If concerns are identified during the study, the participants will be withdrawn.

### Sample size

The sample size of the current trial was calculated based on the following formula [33]:
$$ {\mathrm{n}}_1={\mathrm{n}}_2=\frac{p_1\times \left(1-{p}_1\right)+{p}_2\times \left(1-{p}_2\right)}{{\left({p}_2-{p}_1\right)}^2}\times {\left({\mu}_{\alpha /2}+{\mu}_{\beta}\right)}^2 $$

According to recently published clinical trial results [27], the PASI-50 reached 62.1% (P_1_) in the study group and 35.3% in the control group (P_2_). Therefore, we assumed that the inspection level (α) was 0.05 and the power was 0.8 (β = 1-power = 0.2). For the two-sided tests, 51 participants will be required for each group. Given a 20% loss to follow-up, we expect to require 61 participants for each group. Therefore, this trial will require at least 122 participants.

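### The sample size and its 80% power are worked out for PASI-50, but the primary outcome is PASI-75, so the stated power does not apply to the primary test

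*Protocol article*

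**What the plan says.** Two sections of the protocol article bear on this.

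- **Primary parameters:** "The primary outcome of the RCT is the proportion of patients with a reduction in PASI scores of ≥ 75% compared to baseline", assessed at the 4-week visit. This is PASI-75.
- **Sample size:** the inputs come from a cited trial in which "the PASI-50 reached 62.1" percent in the study group, with "35.3% in the control group (P_2" as the comparator. The section sets out that "the inspection level (α) was 0.05" and that "the power was 0.8 (β = 1-power = 0.2", and concludes: "For the two-sided tests, 51 participants will be required for each group". An allowance for 20% loss brings this to 61 per group and 122 in total.

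No other section closes the gap. Objectives and hypotheses names PASI as the primary endpoint without a threshold. Secondary parameters does not list PASI-50. No PASI-75 rate appears anywhere in the document.

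**The concern.** A sample size calculation supports a trial's primary test only if its inputs describe the primary endpoint. Here the responder definition changes between the two sections. Anyone who reaches PASI-75 has also reached PASI-50, so in the same patients neither arm's PASI-75 rate can exceed its PASI-50 rate. With both rates lower, the absolute difference will usually be smaller too, although that depends on the treatment.

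Two things are at stake. First, the trial may have far less than 80% power for its primary outcome, and a non-significant PASI-75 result could then not be read as evidence of no effect. Second, if the mismatch is left alone, someone could argue after the results are known that PASI-50 was the intended primary outcome, since the sizing supports that reading.

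**Working it through.** **Inputs from the document.** p1 = 0.621, p2 = 0.353 (both labelled PASI-50), two-sided α = 0.05, power 0.80, 1:1 allocation, 51 analysed per group.

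**Step 1: reproduce the plan's figure.** The plan's formula is

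n = [p1(1 − p1) + p2(1 − p2)] / (p1 − p2)² × (z₀.₉₇₅ + z₀.₈₀)²

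- Variance term: 0.621 × 0.379 + 0.353 × 0.647 = 0.2354 + 0.2284 = 0.4638
- Squared difference: 0.268² = 0.0718
- Multiplier: (1.960 + 0.842)² = 7.849
- n = 0.46375 / 0.071824 × 7.849 = 50.68, rounded up to 51

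This matches the plan exactly, and the power at 51 per group by the same formula is 80.2%. The 51 and the 80% therefore belong to the rates labelled PASI-50.

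**Step 2: power for PASI-75 at the same size.** The document gives no PASI-75 rates, so the pairs below are assumptions. Inverting the plan's formula:

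power = Φ( |p1 − p2| / √{[p1(1 − p1) + p2(1 − p2)] / n} − 1.960 )

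Example, 20% vs 5%: the variance term is 0.16 + 0.0475 = 0.2075; 0.15 / √(0.2075 / 51) = 2.352; Φ(2.352 − 1.960) = 65%.

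| Assumed PASI-75, active vs control | Power, 51 per group | Power, 61 per group |
|---|---|---|
| 20% vs 5% | 65% | 73% |
| 25% vs 10% | 53% | 60% |
| 30% vs 15% | 45% | 52% |
| 20% vs 10% | 30% | 35% |

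**Step 3: what 51 per group can detect.** Solving the same formula for 80% power:

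| Assumed control PASI-75 | Active PASI-75 needed | Difference |
|---|---|---|
| 5% | about 24% | about 19 points |
| 10% | about 32% | about 22 points |
| 15% | about 39% | about 24 points |
| 20% | about 45% | about 25 points |

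**Step 4: carry the PASI-50 effect over in three ways.** The PASI-50 rates imply an odds ratio of (0.621/0.379) / (0.353/0.647) = 3.00, a risk ratio of 0.621/0.353 = 1.76 and a difference of 26.8 points. Power at 51 per group by the same formula:

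| Assumed control PASI-75 | Odds ratio kept | Risk ratio kept | Difference kept |
|---|---|---|---|
| 5% | 33.0% | 11.5% | 96.1% |
| 10% | 53.0% | 20.0% | 92.1% |
| 15% | 65.5% | 29.9% | 88.2% |
| 20% | 72.8% | 41.3% | 84.9% |
| 25% | 77.1% | 53.9% | 82.5% |

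Power is below 80% in every row where the odds ratio or risk ratio is kept, and above it in every row where the absolute difference is kept.

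**The case against.** The strongest reply is that the document cannot show that the trial is underpowered. If the 26.8-point difference also held for PASI-75, 51 per group would be enough, so a set of scenarios with differences of 10 to 15 points shows only one side. This is fair as to size, and the full range in Step 4 should be read with it. It does not rescue the stated power, because nothing in the document argues that the difference carries over.

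Four further points deserve an answer.

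- **The arithmetic is correct for its inputs.** True; the fault is the choice of endpoint, not a miscalculation.
- **The Sample size section never mentions PASI-75.** Also true. But it gives 122 as the number the trial requires, with no other justification, so a reader will take the 80% as the power of the primary test.
- **All 61 per group may be analysed,** because the Missing data section counts dropouts as non-success. If the assumed rates are final responder rates with dropouts counted as failures, the four scenarios rise only to between 35% and 73%. If they are rates among completers, counting dropouts as failures dilutes them.
- **One of the two thresholds may be a labelling slip.** Both sections cite the same source, which is not available here. This cannot be excluded. It would change the repair, but one of the two sections would still need correcting.

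**Conclusion.** The concern holds. The 80% power and the 51 per group are derived for PASI-50, while the outcome to be tested is PASI-75. This follows from the two sections alone and does not depend on any assumed rate.

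The effect on power is unknown. Across the assumed PASI-75 rates it runs from about 11.5% to about 96% at 51 per group, and reaching 80% needs a difference of roughly 19 to 25 points for control rates of 5% to 20%. These sizes rest on assumed rates, the plan's unpooled formula and 51 analysed per group. Because the mismatch concerns the primary endpoint and the only justification given for the trial's size, it must be corrected.

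**What to change.** Before any unblinded outcome data are seen:

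1. Go back to the cited source and state which PASI threshold the 62.1% and 35.3% represent, and at what time point.
2. Keep PASI-75 at week 4 as the primary outcome. Replace the PASI-50 inputs with justified PASI-75 rates for both arms.
3. Restate the power that 122 patients give for those rates, or the difference they can detect with 80% power. State the number analysed per group and whether the rates already count dropouts as non-responders.
4. Do not present 80% as the power of the primary test unless the new calculation supports it.

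The alternative is to make PASI-50 at week 4 the primary outcome, with PASI-75 as a key secondary. That would also align the two sections, but it changes the primary endpoint to fit the calculation in a trial that is already recruiting. It is a trade-off with a cost in credibility, and the route above avoids it.

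The cost is a protocol amendment, a registry update and possibly a less favourable stated power. The correction itself adds no patients; if the restated power is low, the report should say so when it interprets a null result.

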### Missing data

The possibility of loss to follow-up has been considered and will be calculated as a part of the sample size estimation. The dropout rates and reason will be recorded. In addition, we will account for other types of randomly missing data by treating dropouts as non-success or non-survival using the intention-to-treat principle.

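### The 20% loss allowance is too small (61 instead of 64 per group), and it does not match an analysis that counts dropouts as non-success

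*Protocol article*

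**What the plan says.** The Sample size section of the protocol article prints a two-proportion formula with unpooled variance and takes its rates from a published trial: "the PASI-50 reached 62.1% (P_1_) in the study group and 35.3% in the control group (P_2"). It sets the error rates ("we assumed that the inspection level (α) was 0.05 and the power was 0.8") and concludes: "For the two-sided tests, 51 participants will be required for each group". It then adds the allowance for attrition, "Given a 20% loss to follow-up, we expect to require 61 participants for each group", and arrives at the total: "this trial will require at least 122 participants". The step from 51 to 61 is not printed.

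The Missing data section first says that loss to follow-up is allowed for in the sample size. It then says that other randomly missing data will be handled by "treating dropouts as non-success or non-survival using the intention-to-treat principle".

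**The concern.** Two things do not fit.

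- **The allowance fails its own condition.** If 51 patients with outcomes are needed and 20% of those randomised are lost, the number randomised must be 51 divided by 0.8. The stated 61 corresponds to multiplying by 1.2, which leaves fewer than 51.
- **The allowance and the analysis rule describe different analyses.** Inflating n makes sense when dropouts are removed and the planned rates hold among those who remain. Counting dropouts as non-success keeps them in the denominator, which lowers both response rates and shrinks the difference between them. A larger n chosen for the first situation does not compensate for the second.

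The stated 80% power is at stake. If the true power is appreciably lower, a null result on the responder endpoint would be hard to interpret.

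**Working it through.** **Inputs.** From Sample size: p1 = 0.621, p2 = 0.353, two-sided alpha 0.05, power 0.80, loss 20%, 51 then 61 per group, 122 in total. From Missing data: dropouts counted as non-success. Allocation is 1:1 (Randomization, allocation, and blinding).

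**1. Reproducing 51.** The printed formula is n = [p1(1−p1) + p2(1−p2)] / (p2−p1)² × (1.960 + 0.842)².

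- Numerator: 0.621 × 0.379 + 0.353 × 0.647 = 0.2354 + 0.2284 = 0.4638
- Denominator: 0.268² = 0.0718
- n = 50.68, rounded up to 51, which agrees with the article.

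**2. The step from 51 to 61.**

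- Multiplying by 1.2: 51 × 1.2 = 61.2, or 50.68 × 1.2 = 60.8. Either is consistent with 61.
- Dividing by 0.8: 51/0.8 = 63.75, or 50.68/0.8 = 63.35. Both round up to 64 per group, 128 in total.
- Check: 61 × 0.8 = 48.8, below 51; 64 × 0.8 = 51.2, which suffices.

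The gap is 3 per group and 6 in total.

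**3. Power with 122 patients if dropouts are excluded.** Power = Φ(|p1−p2|/SE − 1.960), with SE = √{[p1(1−p1) + p2(1−p2)]/n}. At n = 48.8, SE = √(0.4638/48.8) = 0.0975, and Φ(0.268/0.0975 − 1.960) = Φ(0.789) = 78.5%. At 49 per group, the pooled-variance version gives 76% and exact enumeration of the uncorrected chi-square test gives 78%.

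**4. Power with 122 patients if dropouts count as non-success.** Assume the same dropout fraction d in both arms, and that 62.1% and 35.3% are rates among patients with outcomes. Each rate is then multiplied by (1−d), and all 61 per group stay in the analysis. At d = 0.20 the rates are 0.8 × 0.621 = 0.497 and 0.8 × 0.353 = 0.282, and the difference falls from 26.8 to 21.4 percentage points.

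| Dropout in each arm | Rates | Power at 61 per group (article's formula) | Pooled variance | n per group for 80% (article's formula) |
|---|---|---|---|---|
| 5% | 59.0% vs 33.5% | 83% | 81% | 57 |
| 10% | 55.9% vs 31.8% | 79% | 77% | 63 |
| 15% | 52.8% vs 30.0% | 75% | 73% | 70 |
| 20% | 49.7% vs 28.2% | 70% | 68% | 78 |

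The exact chi-square power at 20% is 69%.

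**5. The opposite assumption.** If 62.1% and 35.3% already counted dropouts as failures in the source trial, and attrition here is similar, no inflation is needed. Power at 61 per group is then 86.7% by the article's formula, 85.1% pooled and 86.4% exact.

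**6. Does 64 per group repair both problems?** No. With 20% dropout counted as non-success, under the assumptions of step 4, 64 per group gives 72% (71% pooled). The article's formula needs 77.3, so 78 per group (156 in total); the pooled version needs 81.

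**The case against.** The arithmetic slip is minor. By the article's formula it costs about 1.5 points of power, and the choice between pooled and unpooled variance matters about as much. This objection stands: the slip alone is a correction to a stated figure and does not threaten the trial.

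The larger loss is conditional. A reader might infer that power is simply 70%. The article does not support that as a firm statement, for three reasons.

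- It does not say how the source trial treated dropouts when it arrived at 62.1% and 35.3%. If they were already failures, 122 is more than adequate. That the article inflates for loss at all suggests its authors read these as rates among patients with outcomes, but this is an inference.
- The Missing data section is ambiguous. It deals with loss to follow-up through the sample size and then turns to other kinds of missing data, so the non-success rule could be read as applying only to the latter. The word dropouts points the other way.
- The 70% needs the full 20% attrition, equally in both arms. At 5%, 122 patients are enough.

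Two further readings are tempting and should be left aside. One is that 61.2 was wrongly rounded down. The inflation step is not printed, and the unrounded 50.68 × 1.2 = 60.8 rounds up to 61. The other is that 61 is a legitimate continuity-corrected sample size. That formula does happen to give 61 with no dropout, but the article starts from 51 and attributes 61 to loss to follow-up.

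Finally, the calculation uses PASI-50, whereas the Primary parameters section defines the primary outcome as a PASI reduction of at least 75%. Every figure here will change once that is corrected. This is true, but a recalculation that kept the same dropout step would repeat the error.

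**Conclusion.** The point holds in two parts of unequal certainty.

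- **Firm.** On the Sample size section's own inputs, 61 per group does not leave 51 after a 20% loss. The figure should be 64 per group, and the stated minimum of 122 is short by six. The effect is small: about 78.5% power instead of 80% when dropouts are excluded.
- **Conditional.** The allowance is built for an analysis without dropouts, while the Missing data section keeps them as non-success. If that rule covers loss to follow-up, if dropout is equal in the two arms, and if the planning rates are rates among patients with outcomes, power is about 70% at the planned 20% attrition. Under the alternative assumption about the source rates it is about 85–87%. The article gives no means of choosing between these, so the stated 80% is not tied to the analysis described.

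**What to change.** Choose one analysis and make the sample size match it.

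- **If dropouts count as non-success:** keep 122 and restate the power. Multiply the planned response rates by (1 − dropout) in place of inflating n, and state whether the source rates already include dropouts as failures. Say plainly that the rule applies to loss to follow-up. This costs wording only. If 80% is to be held at 20% dropout with rates among patients with outcomes, about 78 per group (156 in total, 34 more than planned) would be needed on the PASI-50 figures.
- **If dropouts are to be excluded:** correct the stated figure to 51/0.8 = 64 per group (128 in total, six more patients), and amend the Missing data section accordingly.

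Moving to 64 per group while keeping the non-success rule is not a sufficient repair, because power would still be only about 72% under the conditional assumptions above. Make the change in the same revision that reconciles the PASI-50 planning rates with the at-least-75%-reduction primary outcome, so that the calculation is redone once.
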